#### Support people

Support people (ie, family members, significant others and/or carers of eligible and consented people with post-stroke aphasia) will be recruited and consented to participate in this study. Support people will be nominated by people with aphasia and confirmed as potential participants for the study by site champions and speech pathologists within the service in consultation with the treating medical team and the research team. There are no formal inclusion criteria for support people; however, they should play a key role in the person with aphasia’s life and rehabilitation journey. Inclusion of a support person is not a requirement for patients to receive CHAT.

#### Treating clinicians and students

Qualified speech pathologists and allied health assistants employed by the health service who are working in aphasia rehabilitation and delivering treatment as part of the usual care and/or CHAT programme will be eligible to participate. All other relevant staff involved in the delivery of the CHAT programme within their clinical setting (eg, social workers, psychologists, occupational therapists) will also be eligible to participate. Students on placement at participating sites may also be involved and considered eligible. All key treating clinicians and students will be identified based on caseload allocation and invited to participate by principal investigators, site champions or members of the research team prior to and during periods 1, 2 and 3.

#### Non-treating stakeholders

Stakeholders supporting the implementation of the programme within their clinical setting but not involved in the delivery of usual care and/or the CHAT programme will be eligible to participate. This includes speech pathologists and allied health assistants not involved in delivery of usual care and/or the CHAT programme, allied health professionals, nursing staff, administrative and support staff, medical staff, and service/clinical managers supporting the implementation of the CHAT programme at participating sites. All key non-treating stakeholders will be identified and invited to participate in the project by principal investigators, site champions or members of the research team prior to and during periods 1, 2 and 3.

## Outcomes

### Implementation effectiveness

The primary outcome of this study is the proportion of high-quality comprehensive aphasia treatment received, which will be quantified in a composite measure (see tables 2 and 3). This measure of treatment quality is based on research evidence^40^ and stakeholder experience and preferences.^41 42^ Each component (ie, clinical quality of aphasia care indicator) is summarised in a single measure as the proportion of all recommended processes of care received from the total of applicable processes for a patient. The clinical indicators included in the composite measure were developed using a multistakeholder consensus process comprising a two-round e-Delphi exercise and consensus meetings.^41^

**Table 2 T2:** Primary outcome measure: composite measure of quality indicators received

1	Information about *aphasia* is provided to the person with aphasia.
2	Information about *aphasia* is provided to the person with aphasia’s primary carer(s) and/or communication partner(s).
3	Goal setting is undertaken in partnership with the person with aphasia and their primary carer(s) and communication partner(s).
4	The person with aphasia receives comprehensive aphasia therapy (ie, therapy using a range of formats and treatment approaches, including group and individual therapy, and targeting impairment, activity and participation levels of language and communication).
5	The person with aphasia receives high-dose aphasia therapy (ie, >30 hours of aphasia therapy^20^).

**Table 3 T3:** Study implementation and effectiveness outcomes and timings

Measure	Description	Timing
Implementation outcomes and process evaluation measures (as per Proctor *et al* ^61^)		
Composite measure of quality indicators received (Adoption)	*Primary outcome measure. Quantified composite measure of proportion of quality care indicators received. Data triangulated from video/audio recordings of therapy sessions, weekly therapy logs, clinical progress notes and PWA and SP satisfaction and report of receiving each care component.	After 8 weeks of usual care (UC) or Comprehensive, High-dose Aphasia Treatment (CHAT) intervention
Service reach log (Penetration)	No. of CHAT programme enquiries, No. and source of referrals to CHAT. No. of clinicians recruited, clinician demographics, including age, gender, qualification, years of experience, and role/position. No. of people with aphasia and family members/support people recruited, contact details, demographics (including age, gender, occupation and level of education).	Ongoing*
Behavioural determinants survey (Appropriateness, Adoption)	Total and domain scores derived for treating clinicians based on a self-reported survey, recording changes in attitudes, skills, knowledge, and other barriers, and developed using the Theoretical Domains Framework.^53^	Baseline, post-UC/CHAT, follow-up
Semi-structured interviews and/or focus groups (Acceptability, Feasibility, Adoption)	Conducted with a sample of stakeholders from speech pathology, allied health, nursing, and medical professions to explore the CHAT programme’s suitability, usefulness, and feasibility in the clinical context.	Post-UC/CHAT, mid-implementation, follow-up
Satisfaction questionnaire (Acceptability)	To assess clinician satisfaction with the CHAT programme and intention to continue running the programme after study.	At study completion
Mixed methods fidelity evaluation (Fidelity)	Further details to be published separately.	Throughout implementation
Clinical effectiveness outcomes		
Comprehensive Aphasia Test (CAT)	A standardised assessment of language impairment across modalities: comprehension of spoken and written language, repetition, naming, reading and writing. The CAT Modality Mean provides a reliable estimate of the severity of language impairment and is calculated by taking the mean performance across subtest domains.	Baseline, post-UC/CHAT, follow-up
Communicative Effectiveness Index (CETI)	A proxy-rated measure of participants’ functional communication, rated across 16 items representing different everyday communication situations.	Baseline, post-UC/CHAT, follow-up
Communication Confidence Rating Scale for Aphasia (CCRSA)	A patient-reported outcome measure of communication confidence across 10 communication activities.	Baseline, post-UC/CHAT, follow-up
Stroke and Aphasia Quality of Life-39 (SAQOL-39)	A patient-reported outcome measure of health-related quality of life, scored across physical, communication and psycho-social domains.	Baseline, post-UC/CHAT, follow-up
Semi-structured interviews and/or focus groups	Conducted with a sample of people with aphasia post receipt of the CHAT programme to explore experiences of receiving CHAT and satisfaction with the intervention received.	Following participation in the CHAT programme*
Cost-effectiveness outcomes		
Standardised resource utilisation survey	A patient-reported, resource utilisation survey capturing rehabilitation and service usage during intervention periods (UC/CHAT) and follow-up.	Baseline, post-UC/CHAT, follow-up
EQ-5D-5L Health questionnaire	A patient-reported outcome measure of health-related quality of life across five key dimensions: mobility, self-care, usual activities, pain/discomfort and anxiety/depression, for use in economic evaluations.	Baseline, post-UC/CHAT, follow-up

* During period 3 only.

Triangulated data sourcing will allow independent end-point raters to determine whether an indicator has been met. Data sources will include therapy logs, clinical progress notes, and people with aphasia and support person’s report of receiving each care component. A similar composite measure approach has previously been used for assessing the effects of a quality improvement programme of acute stroke care that employed a prospective, controlled, before-and-after study design.^43^ This study design does not allow for participants and assessors to be blinded to group (ie, usual care and CHAT); however, independent endpoint raters, blinded to group, will be trained for the purpose of scoring 100% of the primary outcome measure.

Secondary implementation outcome measures are summarised in table 3 and will include measures related to programme penetration, appropriateness, acceptability, feasibility and fidelity.

### Clinical effectiveness

Given the complex nature of the intervention,^18 44^ multiple secondary outcome measures have been selected to evaluate the clinical effectiveness of CHAT compared with usual care in the different settings, across International Classification of Functioning, Disability and Health^45^ domains (see table 3). Patient-level effectiveness outcomes will examine language impairment (CAT^39^), communication function (Communicative Effectiveness Index (CETI)^46^), communication confidence (Communication Confidence Rating Scale for Aphasia (CCRSA)^47^) and quality of life (Stroke and Aphasia Quality of Life Scale-39 (SAQOL-39)^48^). Clinical effectiveness outcomes will be obtained at baseline, post-usual care or CHAT treatment (2 months) and at follow-up (5 months). Treating and/or independent speech pathologists will conduct the baseline assessment, whereas all post-treatment and follow-up assessments will be conducted by an independent qualified speech pathologist. All assessments will be conducted either at the health service, at the patient’s home or via telerehabilitation, and will be audio and/or video recorded for fidelity checking. Semistructured interviews will also be conducted with people with aphasia at post-therapy, to explore their experience of receiving CHAT and the perceived clinical effectiveness of the programme. The semistructured interviews will be conducted by a member of the research team.

### Sample size

The sample size calculations were conducted based on a secondary outcome measure of clinical effectiveness, due to the lack of existing data for the primary implementation outcome measure. We conducted a Monte Carlo power analysis using data from two sources: the Language Impairment and Functional Therapy trial (ACTRN12613001182785, n=17) and preliminary findings from the implementation of the CHAT programme at the Surgical Treatment and Rehabilitation Service study (ethics approval: HREC/2020/QRBW/50105, n=43). Model parameters were derived from a random intercept model of the effect of treatment on changes in CETI scores, with an estimated treatment effect of 9.08, a random intercept SD of 14.82 and a residual SD of 8.17. To simulate longitudinal data, each participant was assigned three repeated observations. Based on 1000 Monte Carlo iterations, a sample size of 55 participants per group (110 overall) was estimated to yield at least 80% power to detect the specified effect, assuming a two-tailed alpha of 0.05. With a projected attrition of 20%, a total of 138 participants overall (69 per group) is required.

## Data analyses

### Implementation effectiveness

Median regression will be used to compare differences between usual care and CHAT implementation periods for the primary outcome measure, overall composite score: proportion of quality indicators received. The model will be adjusted for patient clustering by service, to protect against residual confounding. Multilevel logistic regression analysis, with levels defined as patients and hospital, to adjust for patient clustering, will be used for dichotomised outcomes such as those relating to individual quality indicators.

Programme reach and quantitative survey data will be analysed using descriptive statistics (eg, m, SD, IQR). For continuous survey data, mean within-group differences will be calculated using paired t-tests and 95% CI. Qualitative data will be analysed using content analysis^49^ and guided by a theoretically grounded approach to analysis of barriers and facilitators to implementation (eg, Theoretical Domains Framework). Comparative analysis will occur between sources (eg, participants, speech pathologists, allied health assistants) to identify common and distinctive themes.

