**Registration details:**

Australian New Zealand Clinical Trials Registry (ANZCTR) prospective registration ACTRN12621001765819. Trial registered 23 December 2021. https://anzctr.org.au/Trial/Registration/TrialReview.aspx?id=381365&isReview=true.

STRENGTHS AND LIMITATIONS OF THIS STUDYA hybrid implementation-effectiveness study design will support a rapid research translation and uptake of the Comprehensive High-dose Aphasia Treatment (CHAT) programme at trial completion by identifying effective implementation strategies that can be tailored to local barriers, and provide concurrent answers about intervention effectiveness in real-world settings.This study will be conducted across six Australian hospitals and health services, to compare the effectiveness and cost-effectiveness of usual care with the CHAT programme, which has been developed to address known aphasia rehabilitation evidence-practice gaps.A diversity of health services will be involved in this study (ie, metropolitan, regional, hospital-based and community-based services), which will allow us to examine implementation in different settings.This study only includes people with post-stroke aphasia who speak English, therefore limiting generalisability to other aetiologies and patients from other linguistic backgrounds.Due to the non-randomised, pre-post design with the allocation of people with aphasia based on time periods, various risks of bias are possible, including selection bias.

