## Methods and analysis

### Design and setting

We will undertake a multicentre, pragmatic, prospective, non-randomised before-and-after study with three study periods (usual care, intervention transition, intervention) and an embedded mixed-methods process evaluation and economic evaluation. A type 3 hybrid implementation-effectiveness design will be employed.^34^ A before-and-after study design was selected over a randomised controlled trial due to requirements of the funding model, and to enable the equitable contribution and participation of partner sites. This study will take place across six hospital and health services, across three Australian states. Sites from a wide range of health service settings will take part in this study (ie, metropolitan, regional, in-patient and out-patient hospital-based and community-based services). The diversity of health services involved in this study will allow us to examine implementation in different settings and to enable us to develop a strong plan for future expansion to more organisations that may seek to implement the CHAT programme within Australia.

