### Clinical effectiveness

Linear mixed modelling will be used to examine whether changes in clinical effectiveness outcomes (ie, CAT, CETI, SAQOL-39, CCRSA), all of which are on interval scale, vary over time as well as across the two groups (usual care and CHAT), after adjusting for the effects of any potential confounders including linear trends over the usual care versus implementation phases. Before modelling the outcomes, baseline characteristics of the two groups will be examined, with any significant differences considered for modelling as covariates to adjust for their possible confounding effects. Collinearity of the covariates will be assessed before including them in the modelling. The results of the linear mixed models will be presented in the form of ORs and their 95% CI. Both intention-to-treat and per-protocol analyses will be conducted. Qualitative interview data will be analysed using thematic analysis.^50^

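### The primary analysis credits clustering by service with protection against residual confounding, but that adjustment cannot remove within-service case-mix or calendar differences between the two periods

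*Protocol article*

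**What the plan says.** All references are to the protocol article.

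- **Primary outcome** (Outcomes, Implementation effectiveness; Table 2): the proportion of applicable care processes that a patient received, built from five indicators.
- **Primary model** (Data analyses, Implementation effectiveness): "Median regression will be used to compare differences between usual care and CHAT implementation periods for the primary outcome measure". The one adjustment named, with its purpose, is: "The model will be adjusted for patient clustering by service, to protect against residual confounding".
- **Secondary clinical outcomes** (Data analyses, Clinical effectiveness): CAT, CETI, SAQOL-39 and CCRSA are modelled "after adjusting for the effects of any potential confounders including linear trends over the usual care versus implementation phases". In addition, "baseline characteristics of the two groups will be examined, with any significant differences considered for modelling as covariates".
- **Design** (Strengths and limitations; Design and setting): the period in which a patient is recruited decides the group. The authors acknowledge that with "allocation of people with aphasia based on time periods, various risks of bias are possible, including selection bias".
- **Calendar** (Study status): usual care recruitment ran from April 2023 to February 2025. The CHAT phase began in April 2025 and is ongoing.
- **Period 1**: services are asked to avoid changes related to CHAT, and unavoidable changes are recorded. No analysis step described in the article uses that record.

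**The concern.** The purpose given for the clustering adjustment is wrong for the main threats in this design. Clustering adjustment answers the question of how alike patients within a service are. Confounding here is a different question: whether the patients and the background care of the CHAT period differ from those of the usual care period within the same service. Residual confounding also normally means what remains after measured confounders have been adjusted for, and the article names none for the primary model.

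One subsection later the article describes a remedy for both threats, but only for the secondary outcomes. As written, the primary comparison is the less protected one.

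At stake is the study's main hypothesis, that implementing CHAT raises quality of care. Case mix can plausibly affect the score: two of the five indicators involve carers or communication partners, a support person is not required, and eligibility leaves room for clinical judgement about comorbidities.

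**Working it through.** **1. The plan's own figure.** No sample size is given for the primary outcome; the one stated is for CETI. With total SD √(14.82² + 8.17²) = 16.92 and effect 9.08, n = 2 × (1.96 + 0.8416)² × 16.92² / 9.08² = 54.5, so 55 per group (power 80.3%). Allowing for 20% attrition, 110 / 0.8 = 137.5, so 138, or 69 per group. This reproduces and is untouched by the present point. The 69 per group is used below.

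**2. What each adjustment can reach.**

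| Source of difference between periods | Allowing for correlation only | Service entered as effects | Baseline covariates | Calendar-time term |
|---|---|---|---|---|
| Changed mix of services | no | yes | in part | no |
| Within-service case-mix shift | no | no | yes, if measured | no |
| Background change in care | no | no | no | yes, if the trend is linear |

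The recruitment windows do not overlap, so period and calendar time are nearly aliased.

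**3. Simulation with no CHAT effect.** Every value here is an assumption except the 69 per group, the six services and the two-year distance between period starts: continuous composite in percentage points, residual SD 15, service SD 8, services balanced, each period about 1.8 years long, linear drift of 0 or 5 points a year, one case-mix covariate worth 8 points per SD and shifted by 0 or 0.5 SD. By arithmetic the expected bias is 5 × 2 = 10 from drift, 8 × 0.5 = 4 from case mix, and 14 from both. Mean period coefficient from median regression (200 runs each):

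| Drift / shift | No adjustment | Service effects only | Service + time + case mix |
|---|---|---|---|
| none / none | 0.30 | −0.01 | 0.94 |
| 5 / none | 9.95 | 9.95 | 0.12 |
| none / 0.5 | 3.61 | 3.57 | 0.02 |
| 5 / 0.5 | 13.66 | 13.52 | 0.07 |

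Service effects left the bias essentially unchanged. The added terms removed it, but the empirical SD of the estimate rose from 3.4–3.9 to 6.7–7.7. In a linear-model proxy, false-positive rates at 0.05 in the four scenarios were 4.5%, 92.5%, 28.5% and 99.8% with service effects only, and 3.7% to 5.5% with the added terms.

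**4. From the mean scale to the planned median.** The table in step 3 treats the score as continuous. With five applicable indicators it moves in steps of 100 / 5 = 20 points. As an illustration, assume five independent indicators with the same probability p of being met:

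- p from 0.35 to 0.45: the chance of at most one indicator met is 0.428 and then 0.256; of at most two, 0.765 and then 0.593. The median is two both times, so the difference is 0.
- p from 0.45 to 0.55: the chance of at most two falls from 0.593 to 0.407. The median goes from two to three, so the difference is 20 points.

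With 69 per group (5,000 simulated trials), the sample medians differed by 0 in 83% of trials in the first case and by 20 points in 89% in the second. The same 10-point background drift can therefore leave no trace or appear as a full step.

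**5. Density of the usual care data.** April 2023 to February 2025 is 23 months. At the planned 69 patients that is 69 / 23 = 3 patients a month across six services.

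**The case against.** **Clustering by service is not useless against confounding.** The services differ in setting, and the transition was spread over August 2024 to June 2025, so services may contribute unequally to the two periods. If service enters as effects, confounding from that changed mix is removed. This stands. The simulation used balanced services and could not show the benefit. A reader might infer that the adjustment protects against no confounding at all; that goes too far.

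**The article is condensed, and covariates may be listed in an analysis plan that is not shown.** This stands as far as it goes: it cannot be inferred that the full plan lacks covariates for the primary model. But the article does state a purpose for the adjustment, and that purpose is wrong. It also writes confounder and trend terms for the secondary outcomes only.

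**Safeguards exist.** A single set of eligibility criteria is stated, with no entry filter specific to tolerating CHAT. Carer items may leave the denominator when they do not apply. Services are asked to hold their model of care steady during usual care. Indicators 4 and 5 (comprehensive therapy; more than 30 hours) are largely built into a 50-hour programme, so drift is a less plausible explanation for them than for indicators 1 to 3. All of this lowers the likely size of the problem without making the stated rationale correct.

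**A time-adjusted model is fragile.** Also right: the time term nearly duplicates period, the SD roughly doubled, and the correction rests on a linear trend. That argues against making the conclusion depend on it, not against showing it.

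**Conclusion.** The concern holds in a limited form. The stated purpose of the clustering adjustment is wrong for within-service case-mix shift and calendar drift, and the article gives the primary comparison less protection than the secondary ones. If either change occurs, part of the primary difference could be wrongly attributed to CHAT.

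The documents give no figure for drift or case-mix shift. A reader might infer that drift and selection will be reported as a CHAT effect, or that the bias is some fixed number of points. Neither is supported. The simulated biases rest on assumed inputs and a continuous score, and on the planned five-item median the result could be nil or a 20-point step. Since two indicators are largely set by the programme, the true contrast may also be large relative to any confounding.

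**What to change.** 1. Limit the clustering sentence to within-service correlation, adding service mix only if service is entered as effects. Drop the general claim about residual confounding.
2. Adjust the primary model for a small set of baseline covariates, fixed in advance and not chosen by significance tests. Examples are baseline aphasia severity, time since stroke, age, setting, and support person yes/no.
3. Report beside it, as a sensitivity analysis and not as a pass/fail gate, the same model with a calendar-time term, and state its linear-trend assumption.
4. Show a descriptive plot of the composite over the usual care period, in intervals wide enough for about 3 patients a month.

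**Cost:** wording, plus a few variables from baseline assessments and clinical records. The time-adjusted model will have a wider interval; in the simulation the SD of the estimate about doubled. The CHAT phase is still running, and covariates named before the outcome data are examined will be more credible than covariates chosen afterwards.

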#### Period 2: intervention transition

The second period of the study will involve the transition in preparation for the implementation of the CHAT programme. This period will include stakeholders, clinicians and students in the same clinical settings which participated in period 1. During the intervention transition, meetings will be conducted with stakeholders and clinicians at each site to identify potential barriers and facilitators to CHAT implementation, identify site champions and tailor the site implementation strategy, as required. Clinicians and students will be upskilled and trained in accordance with the implementation strategy to deliver the CHAT programme to eligible patients with post-stroke aphasia.

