### Process evaluation

An embedded mixed-method process evaluation, with a focus on resource allocation, feasibility and treatment fidelity, will be conducted alongside the main study to provide a complimentary analysis on the potential influence of study processes on outcomes as well as inform clinical feasibility and future scale-up. Study adaptations (planned or unintentional) will be recorded using the Framework for Reporting Adaptations and Modifications to Evidence-based Implementation Strategies.^51^ A behavioural determinants survey will be used to explore changes in clinicians’ knowledge, skills and beliefs about implementing the CHAT programme. These data will be compared pre-training, post-training and post-implementation to evaluate changes across timepoints. Semistructured interviews and/or focus groups will be conducted with clinicians and stakeholders to explore the CHAT programme’s suitability, usefulness and feasibility in the clinical context. Qualitative data from semistructured interviews and/or focus groups will be digitally recorded, transcribed and imported into NVivo to assist with data analysis.^52^ Barriers and enablers identified in the interviews and focus groups will be mapped to the Theoretical Domains Framework.^53^ Process and outcome data will be triangulated across qualitative and quantitative data sources. Evaluation of treatment fidelity will be informed by a conceptual fidelity framework,^54^
^55^ with adaptations to programme delivery explored during interviews or focus groups and through collected intervention data (eg, clinical plans, therapy logs, progress notes, withdrawal forms). Further details on the treatment fidelity protocol will be published separately.

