### Study status

Recruitment for the usual care period of the study was undertaken from April 2023 to February 2025. The intervention transition occurred across health services from August 2024 to June 2025. The CHAT implementation phase commenced in April 2025 and is ongoing.

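### Paired t-tests limit each estimate of change in the staff survey to people who answered at both waves; a mixed model on all responses would be more precise and less exposed to selective staying

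*Protocol article*

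**What the plan says.** The Implementation effectiveness part of Data analyses fixes the method. For continuous survey data, "mean within-group differences will be calculated using paired t-tests and 95% CI". The same paragraph plans descriptive statistics for programme reach and quantitative survey data.

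The repeated staff survey is the behavioural determinants survey. Table 3 describes its output as "Total and domain scores derived for treating clinicians based on a self-reported survey". The Process evaluation section says of it: "These data will be compared pre-training, post-training and post-implementation to evaluate changes across timepoints". Table 3 labels the waves differently (baseline, after usual care or CHAT, follow-up), but both places give three. The clinician satisfaction questionnaire is given once, at study completion, so it cannot be paired.

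On who may respond, the section on treating clinicians and students says that staff are "invited to participate by principal investigators, site champions or members of the research team prior to and during periods 1, 2 and 3", and adds: "Students on placement at participating sites may also be involved and considered eligible". The section on Period 2 describes those taking part as "stakeholders, clinicians and students in the same clinical settings which participated in period 1". That holds the settings constant and does not say that the individuals are the same.

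**The concern.** Staff may join at any stage, and the survey has three waves. Someone who joins after training has no pre-training score, and someone who leaves has no post-implementation score. A paired test drops both from any comparison that needs the missing value. Each estimate of change then describes only the people seen at both waves, and information from the others is lost.

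The article handles its other repeated data differently. The three-wave patient outcomes are analysed with linear mixed models, which can use incomplete sequences. Implementation is the first aim of this type 3 hybrid study, and Table 3 lists the survey under appropriateness and adoption. At stake are the width and interpretation of the intervals for a secondary implementation measure.

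**Working it through.** **Inputs.** The article gives no number of staff, turnover, standard deviation or correlation for the survey, so there is no stated figure to reproduce. The following are assumptions: N responses per wave, a share r of them from people present at both waves (retention), leavers replaced so that each wave still has N responses, equal variance σ² at each wave, and within-person correlation ρ.

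**Precision.** There are m = Nr pairs and s = N(1 − r) single responses at each wave.

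- Paired change: variance = 2σ²(1 − ρ)/m.
- All-data change (generalised least squares, which is what a mixed model approximates): variance = 2σ²/[m/(1 − ρ) + s].
- Ratio of paired to all-data variance = 1 + (1 − ρ)(1 − r)/r. The ratio of standard errors is its square root and does not depend on N.

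Take N = 60, r = 0.5, ρ = 0.5 and σ² = 1. The paired variance is 2 × 0.5/30 = 0.0333. The all-data variance is 2/(30/0.5 + 30) = 2/90 = 0.0222. The ratio is 1.5, and √1.5 = 1.225.

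| Retention r | ρ | Variance ratio | Paired SE larger by |
|---|---|---|---|
| 0.8 | 0.7 | 1 + 0.3 × 0.25 = 1.075 | 3.7% |
| 0.9 | 0.5 | 1 + 0.5 × 0.111 = 1.056 | 2.7% |
| 0.7 | 0.5 | 1 + 0.5 × 0.429 = 1.214 | 10.2% |
| 0.5 | 0.5 | 1 + 0.5 × 1 = 1.5 | 22.5% |
| 0.4 | 0.3 | 1 + 0.7 × 1.5 = 2.05 | 43.2% |

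**Bias.** A simulation of 400,000 people took a true mean change of 0.50 SD and ρ = 0.5. Three rules for staying were tried, the last two with log-odds of staying rising by 1 per SD. The table shows the estimated change when 10%, 30% and 50% leave.

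| Staying depends on | Complete pairs | Likelihood estimate, leavers' first score kept |
|---|---|---|
| Nothing | 0.50 / 0.50 / 0.50 | 0.50 / 0.50 / 0.50 |
| First score | 0.45 / 0.37 / 0.30 | 0.50 / 0.50 / 0.50 |
| The change itself | 0.59 / 0.75 / 0.92 | 0.57 / 0.70 / 0.83 |

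The paired estimate is unbiased when staying is unrelated to scores, too low in one informative case and too high in the other. The likelihood estimate corrects the case that depends on an observed score. It only reduces the bias when staying depends on the unobserved change.

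**The case against.** The strongest defence is that within-person change among staff seen before and after training is a legitimate target. Someone who joined after training has no pre-training state to change from. The planned descriptive statistics can include every respondent, and interviews and focus groups sit alongside. The measure is secondary, and an analysis plan that is not shown may deal with unpaired responses. All of this is fair and keeps the point small. But descriptive statistics give no all-data estimate of change with an interval, and the choice of paired t-tests is made in this document.

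Four stronger readings are tempting, and the documents do not support them.

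- **That the paired change is biased, and in favour of CHAT.** Nothing shows that those who stay are more favourable. A reader might reckon that if half leave and leavers would have changed by 0.5 scale points less, the paired mean is 0.5 × 0.5 = 0.25 points too high. The arithmetic is right, but this is dropout that depends on unseen change, and a mixed model shares most of that error. In the simulation at 50% loss the excess is 0.42 SD for pairs and 0.33 SD for the likelihood estimate.
- **That student placements cause the loss.** Students are eligible for the study, but Table 3 derives the scores for treating clinicians, and no section says that students complete the survey.
- **That the survey waves reach back to the start of the study.** The Study status section says: "Recruitment for the usual care period of the study was undertaken from April 2023 to February 2025". That is patient recruitment. Training belongs to the transition, dated August 2024 to June 2025, so a pre-training wave need not go back to April 2023.
- **That pairing ignores likeness among colleagues.** Differencing within a person already cancels any constant service effect. Only change that differs between services stays correlated.

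**Conclusion.** The point holds as a low-cost improvement. The stated method limits each estimate of change to staff with both scores, in a study that invites staff throughout and surveys them three times. Some unpaired responses are therefore likely, but how many cannot be worked out from the article.

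The precision loss is about 22% in standard error at 50% retention and correlation 0.5. It runs from 4% (80% retention, correlation 0.7) to 43% (40% retention, correlation 0.3). These figures rest on assumed values and on leavers being replaced by new respondents. With 10% replaced and correlation 0.5, the loss is under 3%. Bias is a risk only: it is zero if staying is unrelated to scores, and its direction is unknown otherwise. The primary composite outcome, the patient effectiveness models and the sample size are not touched.

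**What to change.** Replace the sentence on paired t-tests with a linear mixed model for each continuous repeated survey score, using all responses. Fit time point as a three-level fixed effect, service as a fixed effect and a random intercept for clinician. Report the planned contrasts between time points with 95% CI, and keep the paired t-test as a sensitivity analysis. Use one set of labels for the three time points, since Table 3 and Process evaluation word them differently.

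State two limits beside the model. It removes bias from selective staying only if staying depends on observed data. The service main effect does not cover change that differs between services.

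The cost is a change of wording, slightly more analysis work and reliance on a missing-at-random assumption. No extra data are needed: the model needs a stable identifier for each clinician, which pairing already requires. With the CHAT phase still running, the change can be made now.
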